#### IDC-IMPROVE Nurses’ Catheter Care Knowledge and Confidence Scale (KCS-Nurse)

All participating nurses will complete the KCS-Nurse scale at t_0_, t_1_, and t_2_. This scale was developed for this study to assess aged care nurses’ knowledge of, and confidence related to urinary catheters and catheter care. It comprises two sections: confidence and knowledge. The confidence section is theoretically informed by five key competency domains: (1) ability to psychologically support a person living with a long-term urinary catheter; (2) ability to apply clinical decision-making prior to urinary catheterisation; (3) understanding and application of principles for inserting and/or removing a urethral or suprapubic catheter; (4) knowledge and application of evidence-based nursing interventions to promote physical well-being; and (5) ability to minimize and troubleshoot common issues related to long-term urinary catheterisation. This section includes 21 statements regarding nursing actions specific to catheter care and uses a 5-point Likert scale (ranging from 0 for “no confidence” to 5 for “high confidence”) to capture responses; the highest possible score for these 21 statements is 105. The knowledge section includes 30 items with a dichotomous measurement scale, where a correct answer scores 1 and an incorrect or uncertain answer scores 0, resulting in a highest possible score of 30. A survey of 11 experts conducted by the research team has already demonstrated strong content validity (S-CVI/Ave = 0.97). Internal validity, construct validity, and convergent validity of the scale will be estimated in this study.

#### IDC-IMPROVE Personal Care Worker Catheter Care Knowledge and Confidence Scale (KCS-PCW)

All participating PCWs will complete the KCS-PCW scale at t_0_, t_1_, and t_2_. The scale was developed for this study to assess PCWs’ confidence and knowledge regarding urinary catheters and catheter care. The confidence section includes 14 statements encompassing four domains: (1) ability to emotionally support a person living with a urinary catheter; (2) understanding of the basic structure and function of the lower urinary tract; (3) understanding of the purpose, main types, and reasons why a person may need a urinary catheter; and (4) knowledge of the role of the personal care worker caring for a person living in a residential aged care home who has a urinary catheter. This section uses a 5-point Likert scale to capture responses, ranging from zero (no confidence) to five (high confidence), with the highest possible score for the 14 statements being 70. The knowledge section consists of 20 items with a dichotomous measurement scale where a correct answer scores 1 and an incorrect answer scores 0, resulting in a highest possible score of 20.

### Secondary outcomes

The secondary outcomes include data likely to be used in a larger definitive trial to test the effectiveness of the intervention. The compatibility of the *Bundle* with current residential aged care catheter care practices, procedures and policies will be assessed through a pre- and post-intervention audit of each residential aged care home IDC-related organisational policies and practices, as well as post-intervention semi-structured interviews with managers/senior leaders about their organisational IDC policies and practices.

Pilot data on the preliminary effects of the *Bundle* on rates of IDC-related complications will be assessed through a pre- and post-retrospective review of medical records of residents with an IDC. Records will be reviewed for incidences of CAUTI (symptomatic and asymptomatic), catheter blockages, catheter-related trauma, leakage/bypassing, and hospitalisations related to catheter complications. Pilot data on the effects of the *Bundle* on nurses’ knowledge and confidence providing IDC care will be assessed through the *Nurses’ Catheter Care Knowledge and Confidence Scale* (KCS-Nurse), a study-specific survey of nurses’ knowledge and confidence.

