## Background

Indwelling urinary catheters (IDCs) are devices inserted into the bladder via the urethra or lower abdomen (suprapubic region) and remain in place to aid urine drainage. International estimates suggest between 5 and 8% of people in long-term care homes have an IDC [1–3]. During 2022–2023, 8.4% (15,249) of people receiving government subsidised residential aged care in Australia required some form of catheter care [4].^1^

Although potentially beneficial, IDC use is associated with higher risks of morbidity [5, 6]. IDCs provide a mechanism for bacteria to enter the bladder and therefore people with an IDC are at risk of developing a catheter-associated urinary tract infection (CAUTI). The longer a catheter remains in place, the higher the risk. The European Association of Urological Nurses (EAUN) defines long-term catheterisation as the use of a catheter remaining in situ for ≥ 14 days [7]. CAUTIs can lead to other complications such as encrustation and catheter blockage [8], for which treatment is challenging [9]. CAUTIs and catheter blockages are serious events that may result in presentation to emergency departments [10]. Transferring older people from aged care homes to emergency departments or hospital admission has been associated with further risks, including delirium, increased functional decline, nosocomial infections, and pressure injuries [11, 12].

Projections from the Australian Institute of Health and Welfare (AIHW) and Australian Bureau of Statistics (ABS) show that Australia’s population over 65 will continue to grow substantially over the coming decades, driven by increased life expectancy and lower birth rates [13]. By 2066, it is estimated that around 23% of the population will be over 65. As this demographic shift progresses, age-related health issues—including conditions that may necessitate long-term use of medical devices like IDCs—are expected to rise due to increased healthcare demands among older individuals.

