This trend will likely impact the aged care sector, as a significant portion of the older population transition into aged care homes. In these settings, residents often have complex health needs requiring specialised care and skilled staff, particularly for indwelling catheter management and other chronic care interventions. Meeting this demand will necessitate upskilling the workforce through education and training in IDC care and related areas to provide appropriate support and prevent complications associated with long-term use.

The day-to-day care of people with IDCs in aged care homes in Australia is undertaken by personal care workers (PCWs) and registered and enrolled nurses. This workforce is central to the quality and safety of care in residential aged care homes. The Australian Royal Commission into Aged Care Quality and Safety heard evidence of poor quality, unsafe practices related to IDCs and called for interventions to strengthen the capacity of this workforce to care for older Australians [14].

Through the *Improving indwelling urinary catheter care in residential aged care* (IDC-IMPROVE) project, we aim to improve knowledge and skills in catheter care among the residential aged care workforce. Specifically, we aim to support nurses to perform routine uncomplicated catheter exchanges on site; identify, prevent and manage IDC-related problems; and recognise and address the inappropriate use of an IDC.

We have designed and validated a comprehensive, evidence-based intervention titled the *IDC-IMPROVE Catheter Care Bundle* (hereafter referred to as the *Bundle*). The *Bundle* was developed in consultation with key stakeholders and with reference to the most recent comprehensive evidence-based guidelines from the EAUN [7] about urinary catheter management. It has been adapted to suit residential aged care nursing and care staff. The *Bundle* consists of the following:Principles for person-centred catheter careAn online course for registered and enrolled nurses about person-centred IDC careAn online course for PCWs about person-centred IDC care.A catheter care toolkit for managers/senior leaders.

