## Methods

The aims of this study are to determine the feasibility of implementing the *Bundle* in residential aged care homes and to determine the utility and feasibility of a definitive phase III trial to assess its effectiveness. The aims are encompassed by the following five objectives:To determine the acceptability of the *Bundle* to end users in residential aged care homes.To explore the fidelity of the implementation of the *Bundle*.To investigate the compatibility of the *Bundle* with current catheter care practices, procedures and policies.To investigate the internal consistency, construct validity and convergent validity of a scale developed to measure nurses’ knowledge and confidence to provide person-centred IDC care.To gather descriptive pilot data related to rates of IDC-related complications, and staff knowledge and confidence to provide person-centred IDC care.

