t_0_, t_1_	X	X	IDC-IMPROVE Clinical Data Extraction Form	Clinical information about age range, gender, IDC type, reason for IDC, duration of IDC, number of IDC changes, disciplinary background of staff who perform the change, number and type of IDC-related complications, and number of admissions to hospital and emergency departments for IDC-related complications for residents with an IDC for the prior 3 months, to be completed by managers/senior leaders or RNs
Feasibility and sustainability data collection tools				
t_0_, t_2_	X	X	IDC-IMPROVE Catheter Care Audit Tool	A pre and post intervention audit of each aged care home, IDC-related organisational policies and practices, to be completed by managers/senior leaders and administered with the aged care home demographic survey
t_0_, t_1_, t_2_	X		Participant Completion and Withdrawal Record	Number of nurses and PCWs who enrol, complete or withdraw from the education or application to practice phase
t_1_	X		Online Catheter Care Course for Nurses Feedback Survey	Rating scale to capture nurses’ satisfaction with the content and questions on their experience of the course
t_1_	X		Catheterisation Skills Workshop Feedback Survey	An online survey nurses will be asked to complete at the end of the catheterisation skills workshop
t_2_	X		Semi-structured qualitative interviews	Interviews will be conducted with nurses, PCWs and managers exploring participants’ perspectives and experiences with the *Bundle*, barriers and enablers to implementing the trial, contextual factors affecting IDC care and implementation of the *Bundle*

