### Data analysis

Feasibility outcomes will be analyzed using quantitative and qualitative approaches. The R software program will be used for all quantitative data manipulation and analysis. Descriptive analysis will be conducted for all demographic and scaled outcomes, reporting at baseline (t_0_), post-intervention (t_1_), and follow-up (t_2_) timepoints. The KCS-Nurse scores will be assessed for normality using descriptive statistics and histograms. All subscale scores will be analysed using the median with the 25th and 75th percentiles (IQR), and normally distributed scores will be additionally analysed with means and 95% confidence intervals (CI). Discrete and categorical data will be analysed using frequencies with relative frequencies. Descriptive analyses will be assessed according to progression criteria and reported against the prescribed thresholds in Table 3.

Survey feedback will be summarised. Qualitative interview data will be recorded, transcribed verbatim, checked for accuracy, and analysed using thematic analysis [21]. Two members of the research team will analyse the data independently and conduct a thematic analysis. Qualitative findings will be used alongside the analysis of progression criteria and feedback from surveys to conduct a process evaluation. This will explore how the intervention was experienced by participants and any changes that they think would improve the trial and intervention and their implementation. A “Framework” analytical approach [22] informed by the 14-domain version of the Theoretical Domains Framework [23] and based on the research objectives will be used to describe the feasibility of the *Bundle*.

The internal consistency, construct validity and convergent validity of the KSC-Nurse will be analysed. Internal consistency will be estimated using Cronbach’s alpha. Construct validity will be estimated using confirmatory factor analysis (CFA), based on the 5 key competency domains of the scale. The model fit will be assessed using the Comparative Fit Index (CFI). Convergent validity will be estimated by calculating the Pearson correlation coefficient between the KSC-Nurse and the Nurse Professional Competence Scale-Short Form (NPC Scale-SF) [24], accounting for clustering. The intra-cluster coefficient (ICC) will be calculated based on KSC-Nurse scores to explore clustering effects and inform implementation of the instrument in other studies.

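### Complication rates are promised, but the only summary stated for such counts is a frequency with no catheter-time denominator

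*Protocol article*

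**What the plan says.** The fifth objective in Methods is "To gather descriptive pilot data related to rates of IDC-related complications". The Secondary outcomes section repeats the target, with pilot data on preliminary effects: "rates of IDC-related complications will be assessed through a pre- and post-retrospective review of medical records of residents with an IDC". It then lists the events: "Records will be reviewed for incidences of CAUTI (symptomatic and asymptomatic), catheter blockages, catheter-related trauma, leakage/bypassing, and hospitalisations related to catheter complications".

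Table 1 describes the Clinical Data Extraction Form, completed at t0 and t1 in both arms. It takes the number and type of complications, and also "duration of IDC, number of IDC changes", "for residents with an IDC for the prior 3 months".

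In the Data analysis section, the one sentence that reaches event counts is general: "Discrete and categorical data will be analysed using frequencies with relative frequencies". Neither catheter-days nor any other person-time denominator is named in the article.

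Two Background statements bear on exposure. On infection risk: "The longer a catheter remains in place, the higher the risk". Among the project's specific aims for nurses, after on-site exchanges and handling catheter problems: "recognise and address the inappropriate use of an IDC".

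**The concern.** A rate needs a denominator in time. A frequency with a relative frequency has none. Because the form records the number of events, one resident can contribute several, so a relative frequency could mean a share of residents or a share of events. Neither is a rate.

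The difference matters only if catheter time varies. A resident may be catheterised for part of the window because the device was inserted late, removed early, or the resident left the home. If average catheter time differs between arms, or between t0 and t1, events per resident will differ with no change in risk per day catheterised. The Bundle could itself contribute, since it addresses inappropriate use.

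The set of residents is also unclear. The Table 1 phrase can mean residents with a catheter at extraction, residents catheterised throughout the window, or anyone catheterised during it. On the first two readings, a resident whose catheter was removed drops out.

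At stake is the quality of the pilot complication figures, which the Secondary outcomes section places among data likely to be used in a definitive trial.

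**Working it through.** **Plan's own figure.** None exists on this point. The only sample-size calculation concerns nurses (62, for a completion proportion). It reproduces as 1.96² × 0.80 × 0.20 / 0.10² = 61.46, rounded up to 62, but has no bearing on resident complications.

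**Inputs.** From the documents: a three-month look-back at t0 and t1. Assumed, because the documents give no values: a 90-day window, a constant daily risk, a reference mean exposure of 90 catheter-days, and a true rate of 5 per 1000 catheter-days (varied from 2 to 10).

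**Formulas.** Expected events per resident = rate × catheter-days. Proportion with at least one event = 1 − exp(−rate × catheter-days), with every resident given the mean exposure. The rate per catheter-day is held equal, so its ratio is 1.00 throughout.

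| Mean catheter-days | Ratio of events per resident (vs 90) | Residents with ≥1 event, at 5 per 1000 | Ratio of proportions | Rate ratio |
|---|---|---|---|---|
| 90 | 1.00 | 36.2% | 1.00 | 1.00 |
| 80 | 80/90 = 0.89 | 33.0% | 0.910 | 1.00 |
| 70 | 70/90 = 0.78 | 29.5% | 0.815 | 1.00 |
| 60 | 60/90 = 0.67 | 25.9% | 0.715 | 1.00 |
| 45 | 45/90 = 0.50 | 20.1% | 0.556 | 1.00 |

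The ratio of events per resident does not depend on the assumed rate. The ratio of proportions does: at 70 days it runs from 0.79 (2 per 1000) to 0.85 (10 per 1000).

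**How much removal this implies.** Suppose removal halfway through the window were the only cause of lost time, each removal costing 45 days. Removing 20% of catheters loses 0.20 × 45/90 = 10% of catheter-days. A mean of 80 days needs (90 − 80)/45 = 22% removed; 70 days needs 44%; 60 days needs 67%; 45 days needs every catheter removed halfway. The lower end of the table is therefore an extreme, not an expectation.

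**When nothing changes.** With equal mean exposure, the ratio of events per resident equals the rate ratio.

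**The case against.** The strongest reply has four parts.

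1. **The article is condensed and the analysis plan is not shown.** The sentence on discrete data is generic, and the denominator may be defined elsewhere. That lowers the weight of the point but does not remove it: the article names a rate as the target and states a summary that is not one. Dates missing from the form also cannot be recovered by a later analysis plan.

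2. **Exposure is partly handled by design.** A common window standardises follow-up to some degree, and duration is collected. This stands. A reader might infer that catheter time is disregarded altogether; that is true only of the stated analysis. One reading of the Table 1 phrase even implies full-window exposure for everyone.

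3. **The Bundle is not described as shortening catheterisation.** This also stands. A reader might infer that reducing catheter time is a purpose of the intervention. The text speaks only of recognising and addressing inappropriate use, and neither removal nor duration is listed as an outcome. Timing further weakens a removal scenario: the post-workshop survey is also a t1 instrument, and the three-month practice phase follows the course and workshop, so the t1 look-back may mostly precede changed practice. The Table 2 timeline is not available to settle this.

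4. **A per-resident measure is legitimate.** Fewer complications because an unneeded catheter was removed is a real benefit, which a rate per catheter-day hides. This is right, and is why both should be reported. It also rules out saying that the per-resident figure is useless for planning: it serves if the definitive trial adopts that endpoint.

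**Conclusion.** The point holds as a mismatch between a stated target (rates) and the only stated summary for counts (frequencies), with no exposure denominator and an unclear resident set. Its possible size, on assumed exposures of 80 to 45 days against 90, is a ratio of events per resident of 0.89 to 0.50 when the rate ratio is 1.00; it is nil if exposure is equal. The 1.00 assumes constant daily risk. If risk rises the longer a catheter has been in, the rate per catheter-day also depends on duration, which is a further reason to show duration beside it.

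A reader might infer that the feasibility conclusion is compromised. The documents do not support that: the complication data are descriptive, no hypothesis test on them is stated, and Table 3 uses the extraction form only for completeness of data collection. Nor do they show that residents whose catheter was removed will be excluded; they leave it open. The consequence is confined to the pilot estimates passed to a definitive trial. The change is worth making because it is cheap.

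**What to change.** - **Data analysis section:** for each complication, report events per 1000 catheter-days by arm and period, with a 95% confidence interval that allows for clustering by home. Give the per-resident frequency alongside, saying whether it counts residents or events.
- **Denominator:** take catheter-days from the duration of catheterisation, truncated to the three-month window.
- **Resident set:** state that every consented resident with a catheter at any time in the window is counted, including those whose catheter was removed. Report removals separately, by arm and period.
- **Form:** record insertion and removal dates within the window, since a single duration entry may not give the days that fall inside it.

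**Cost:** wording, plus dates on a form already in use; no additional homes or staff participants. The Residents section seeks consent from residents who have a catheter, so the team should check that the consent covers records after removal, and report any residents with a catheter in the window who could not be included.

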### Data analysis

Feasibility outcomes will be analyzed using quantitative and qualitative approaches. The R software program will be used for all quantitative data manipulation and analysis. Descriptive analysis will be conducted for all demographic and scaled outcomes, reporting at baseline (t_0_), post-intervention (t_1_), and follow-up (t_2_) timepoints. The KCS-Nurse scores will be assessed for normality using descriptive statistics and histograms. All subscale scores will be analysed using the median with the 25th and 75th percentiles (IQR), and normally distributed scores will be additionally analysed with means and 95% confidence intervals (CI). Discrete and categorical data will be analysed using frequencies with relative frequencies. Descriptive analyses will be assessed according to progression criteria and reported against the prescribed thresholds in Table 3.

Survey feedback will be summarised. Qualitative interview data will be recorded, transcribed verbatim, checked for accuracy, and analysed using thematic analysis [21]. Two members of the research team will analyse the data independently and conduct a thematic analysis. Qualitative findings will be used alongside the analysis of progression criteria and feedback from surveys to conduct a process evaluation. This will explore how the intervention was experienced by participants and any changes that they think would improve the trial and intervention and their implementation. A “Framework” analytical approach [22] informed by the 14-domain version of the Theoretical Domains Framework [23] and based on the research objectives will be used to describe the feasibility of the *Bundle*.

The internal consistency, construct validity and convergent validity of the KSC-Nurse will be analysed. Internal consistency will be estimated using Cronbach’s alpha. Construct validity will be estimated using confirmatory factor analysis (CFA), based on the 5 key competency domains of the scale. The model fit will be assessed using the Comparative Fit Index (CFI). Convergent validity will be estimated by calculating the Pearson correlation coefficient between the KSC-Nurse and the Nurse Professional Competence Scale-Short Form (NPC Scale-SF) [24], accounting for clustering. The intra-cluster coefficient (ICC) will be calculated based on KSC-Nurse scores to explore clustering effects and inform implementation of the instrument in other studies.

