### Feasibility cRCT

This is a multi-centre, facility-level cluster randomised control feasibility trial with an embedded process evaluation conducted in residential aged care homes in Australia. After baseline data are collected for all outcome measures, 12 aged care homes will be randomised to receive the intervention and 12 will continue to provide usual practice (control). Each cluster comprises one site (residential aged care home). The control sites are included to assess acceptability of randomisation and fidelity to data collection and to provide a comparator for pilot data. Control sites will receive some elements of the *Bundle* after the trial closes and data collection is completed at their site. Figure 1 provides an overview of the trial.

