**Table 2 Tab2:**
[figure not shown]
Timeline of study procedures, including enrolment, interventions, and assessment points

**Table 3 Tab3:** Criteria, data collection methods, and thresholds for progression to a definitive trial

Criteria	Data collection	Threshold
(ii) Acceptability of the bundle	• Feedback surveys • Audit tool • Qualitative interviews	• 75% + participants “satisfied” or “very satisfied” • Thematic analysis of qualitative interviews • Descriptive analysis of audit tool
(iii) Fidelity of implementation	• Participant completion and withdrawal record • KCS-Nurse • KCS-PCW • NPC-Scale-SF • Clinical data extraction form	• Site retention: 20 sites complete all trial phases • Participant retention: ≥ 80% of enrolled participants complete all study follow-ups (t_0_, t_1_, t_2_) • Fidelity to data collection: 75% of all *expected* data points collected across KCS-Nurse, KCS-PCW, NPC-Scale-SF, and Clinical Data Extraction Forms from sites and participants who complete all trial phases • Internal Consistency of KCS-Nurse: Achieves acceptable internal consistency
(iv) Compatibility of bundle with standard practice	• Qualitative interviews • Audit tool	• Thematic analysis of qualitative interviews • Descriptive analysis of audit tool

Prior to site randomisation, information will be collected from organisations on their size, ownership and staffing, and from individual nurses and PCWs in terms of their qualifications, years in nursing and in working in residential aged care. The research team will provide sites with extraction forms to obtain key information from the medical records of residents with IDCs who consent to participate in the study. Research staff will be trained in obtaining informed consent and in the use of the extraction forms prior to inviting residents to participate. We anticipate some participating nurses may complete the online course but will be unable to complete a workshop due to workshop capacity limitations. These nurses will be flagged, and their outcome data will not be combined with workshop participants’ data.

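### KCS-Nurse and KCS-PCW scores are planned only as separate summaries at t0, t1 and t2, so the pilot data will not describe change in the same staff or use each person's baseline

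*Protocol article*

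**What the plan says.** The scale sections set up repeated measurement of the same people: "All participating nurses will complete the KCS-Nurse scale at t_0_, t_1_, and t_2", and "All participating PCWs will complete the KCS-PCW scale at t_0_, t_1_, and t_2". The baseline score exists before allocation (Feasibility cRCT): "After baseline data are collected for all outcome measures, 12 aged care homes will be randomised".

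The Data analysis section then fixes the form of reporting: "Descriptive analysis will be conducted for all demographic and scaled outcomes, reporting at baseline", followed by the post-intervention and follow-up time points. Subscales get a median with quartiles, and normally distributed scores also get a mean with a 95% CI. The section names no change within a person, no common set of people across time points and no baseline-adjusted contrast.

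Two other statements bear on this. Secondary outcomes says that the KCS-Nurse will provide pilot data on the effects of the Bundle, and that the secondary outcomes include data likely to be used in a larger trial. Table 3 sets the retention threshold: "Participant retention: ≥ 80% of enrolled participants complete all study follow-ups". Loss of up to 20% therefore counts as success.

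**The concern.** Separate summaries describe a group at three moments. They do not describe what happened to its members. Two things are at stake.

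- **Planning information.** A definitive trial that uses baseline scores needs the correlation between baseline and follow-up, or equivalently the SD of change. Neither can be recovered from time-point medians, quartiles, means and CIs. The difference between two means equals the mean change only if the same people contribute to both, and the difference between two medians is not the median change.
- **Interpretation.** If the t0 summary holds everyone enrolled and the later ones hold only those still responding, the difference mixes real change with a change in who answers. Staff who leave may differ in knowledge or confidence from those who stay. Nurses who miss the workshop are also to be kept apart from workshop participants (Outcome measures), which can further alter who is summarised in the intervention arm.

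**Working it through.** **Inputs from the article.** Retention threshold 80%; 96 nurses in 24 homes, 12 per arm, so about 48 nurses per arm; same staff at t0, t1 and t2. **Not in the article, so assumed:** the score gap between leavers and stayers, and the correlation r between baseline and follow-up. Results are in units of the score SD.

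**1. The plan's own figure.** n = 1.96² × 0.80 × 0.20 / 0.10² = 61.46, rounded up to 62. The stated 62 nurses reproduces. It concerns a completion rate and does not depend on how scores are summarised.

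**2. What time-point summaries leave unknown.** With equal SDs at both visits, the SD of change is sqrt(2(1 − r)). For r = 0.3, 0.5 and 0.7 this is 1.18, 1.00 and 0.77 SD. The same time-point summaries fit all three. Baseline adjustment multiplies the variance of a between-arm contrast by 1 − r²: 0.91, 0.75 and 0.51, a saving of 9%, 25% and 51%. With 38 nurses per arm (48 × 0.8 = 38.4) and clustering ignored, the unadjusted 95% half-width is 1.96 × sqrt(2/38) = 0.45 SD. Adjusted, it is 0.43, 0.39 and 0.32 SD.

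**3. Apparent rise with no learning.** If a share d leaves and leavers score g below stayers, the stayers' mean exceeds the full-group mean by d × g. With d = 0.20:
- g = 0.3 gives 0.06 SD
- g = 0.5 gives 0.10 SD
- g = 0.25 to 1.0 gives 0.05 to 0.20 SD

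This takes the gap as persisting in full at follow-up. If loss depends on the t0 score alone and r = 0.6, the follow-up shift is 0.6 times as large: 0.6 × 0.06 = 0.036 and 0.6 × 0.10 = 0.06 SD.

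**4. Simulation.** No learning, 80% retained, r = 0.6, drop-out depending on the t0 score with log-odds b per SD:

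| b | Follow-up mean of stayers minus full t0 mean | Raw change in stayers | After conditioning on t0 |
|---|---|---|---|
| 0.5 | 0.06 | −0.04 | about 0 |
| 1 | 0.10 | −0.07 | about 0 |
| 2 | 0.16 | −0.10 | about 0 |

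With b = 1 in both arms the shift is 0.10 in each and cancels in the comparison. With b = 1 or 2 in the intervention arm only, 0.10 or 0.16 SD remains as a false difference.

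**5. Precision of pairing.** With 20% lost, paired change has variance 2(1 − r)/(0.8N) = 2.5(1 − r)/N. Treating the two time points as independent gives 1/N + 1/(0.8N) = 2.25/N. The SE ratio sqrt(2.5(1 − r)/2.25) is 0.82, 0.67 and 0.58 at r = 0.4, 0.6 and 0.7.

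**The case against.** The strongest defence is that this is a descriptive feasibility trial reported in a condensed article. Objective 5 asks for descriptive pilot data on knowledge and confidence and does not mention change. No effect test is planned. In Table 3 the scales count only towards data completeness and, for the KCS-Nurse, internal consistency. A control arm is there as comparator. A full protocol or analysis plan may add change tables. The possible shift is also small: one arm's mean from 38 nurses has a 95% half-width of 1.96/√38 = 0.32 SD before clustering. Staff are recruited on the basis that they plan, or are expected, to remain at the site.

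Most of this stands and limits the size of the point. It does not remove it. The Data analysis section is specific elsewhere (Cronbach's alpha, confirmatory factor analysis, a correlation accounting for clustering, the ICC), and for the repeated scores it states a form of reporting that does not link them. Secondary outcomes speaks of effects and of a larger trial, which time-point summaries serve poorly.

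Some stronger readings are tempting but are not supported:
- *The plan gives a biased picture of change.* The article does not say whether each summary uses all respondents or only completers. The bias is possible, not built in.
- *The baseline is not used.* It is reported. It is not used as a paired or adjusting value.
- *Pairing cuts the standard error by sqrt(1 − r).* That holds for equal numbers at both visits. With 20% lost the gain is smaller, as in step 5.
- *Change in completers cures the problem.* Step 4 shows that it can be biased the other way by regression to the mean.
- *The anonymised transfer breaks the link between visits.* Judging retention across t0, t1 and t2, and correlating the KCS-Nurse with the NPC scale, already need person-level records.

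**Conclusion.** The point holds as a missed use of data already being collected. As published, the plan will not deliver the SD of within-person change or the t0-t2 correlation, and it delivers the mean change only if the same staff contribute at each visit. A false rise of about 0.06 to 0.10 SD within an arm is possible. That figure rests on three assumptions: each summary uses whoever responded, 20% are lost, and leavers score 0.3 to 0.5 SD below stayers at follow-up as well as at t0. It carries into the comparison between arms only if selective loss differs between arms. No stated figure is wrong and no progression criterion depends on it. Severity is low to moderate.

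**What to change.** In Data analysis, keep the time-point summaries and add, for the KCS-Nurse and KCS-PCW, by arm and labelled exploratory:

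1. Within-person change t1 − t0 and t2 − t0 in staff with both scores: median and IQR, and mean, SD and 95% CI allowing for home. Report the t0-t2 correlation alongside.
2. The t0 scores of staff with and without follow-up scores, so that readers can see whether loss was selective and whether it differed between arms.
3. A baseline-adjusted difference between arms with a 95% CI allowing for clustering by home. This is needed because raw change in completers can itself be biased.

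The adjusted difference removes the distortion when loss depends on the t0 score. It does not protect against loss that depends on the unseen follow-up score.

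The cost is a few sentences of analysis text and a few lines of R. No new data, sample size or threshold is affected.
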